# A randomized crossover study of functional electrical stimulation during walking in spastic cerebral palsy: the FES on participation (FESPa) trial

**DOI:** 10.1186/s12887-021-03037-9

**Published:** 2022-01-13

**Keywords:** Cerebral palsy, Spasticity, Gait, Orthoses, Functional electrical stimulation, Goal attainment scale

## Abstract

**Background:**

Spastic cerebral palsy is the most common cause of motor disability in children. It often leads to foot drop or equinus, interfering with walking. Ankle-foot orthoses (AFOs) are commonly used in these cases. However, AFOs can be too restrictive for mildly impaired patients. Functional electrical stimulation (FES) of the ankle-dorsiflexors is an alternative treatment as it could function as a dynamic functional orthosis. Despite previous research, high level evidence on the effects of FES on activities and participation in daily life is missing. The primary aim of this study is to evaluate whether FES improves the activity and participation level in daily life according to patients, and the secondary aim is to provide evidence of the effect of FES at the level of body functions and activities. Furthermore, we aim to collect relevant information for decisions on its clinical implementation.

**Methods:**

A randomized crossover trial will be performed on 25 children with unilateral spastic cerebral palsy. Patients aged between 4 and 18 years, with Gross Motor Functioning Classification System level I or II and unilateral foot drop of central origin, currently treated with AFO or adapted shoes, will be included. All participants will undergo twelve weeks of conventional treatment (AFO/adapted shoes) and 12 weeks of FES treatment, separated by a six-week washout-phase. FES treatment consists of wearing the WalkAide® device, with surface electrodes stimulating the peroneal nerve during swing phase of gait. For the primary objective, the Goal Attainment Scale is used to test whether FES improves activities and participation in daily life. The secondary objective is to prove whether FES is effective at the level of body functions and structures, and activities, including ankle kinematics and kinetics measured during 3D-gait analysis and questionnaire-based frequency of falling. The tertiary objective is to collect relevant information for clinical implementation, including acceptability using the device log file and side effect registration, cost-effectiveness based on quality adjusted life years (QALYs) and clinical characteristics for patient selection.

**Discussion:**

We anticipate that the results of this study will allow evidence-based use of FES during walking in children with unilateral spastic cerebral palsy.

**Trial registration:**

ClinicalTrials.gov: NCT03440632.

**Supplementary Information:**

The online version contains supplementary material available at 10.1186/s12887-021-03037-9.

## Background

### Spastic cerebral palsy

Motor disability in children is most frequently caused by cerebral palsy (CP), with an incidence of 1.8 to 2.1 children per 1000 births [1, 2]. CP is defined as ‘a group of permanent disorders of the development of movement and posture causing activity limitations, resulting from an injury in the developing central nervous system’ [3–5]. In the domain of activity (based on the International Classification of Functioning, Disability and Health (ICF)), the Gross Motor Function Classification System (GMFCS) distinguishes patients with CP classified as level I (walking independently) to level V (wheelchair bound) [6, 7]. In the ICF domain of body functions and structures, the anatomical distribution (e.g. bilateral or unilateral) and the motor abnormality (i.e. spastic, dyskinetic or ataxic) are important characteristics of CP [7]. Spastic CP is the most common type of CP.

Spasticity is defined as ‘a motor disorder characterized by a velocity-dependent increase in tonic stretch reflexes (muscle tone) with exaggerated tendon jerks, resulting from hyperexcitability of the stretch reflex, as one component of the upper motoneuron syndrome’ [8, 9]. Mobility in general - and walking in particular - is often negatively affected by spasticity. Its impact can manifest in such forms as drop foot or true equinus, which can be caused by spasticity of the ankle plantar flexors (e.g. the gastrocnemius and soleus muscle), and weakness and poor selective control of the ankle dorsiflexors (e.g. the anterior tibial muscle) [10]. Consequently, patients with CP often experience fatigue, resulting in limited walking distance with subsequent a reduced physical activity level and impaired health status. Physical activity is suggested to be lower in young people with CP than in typically developing peers [11]. Patients with CP also experience an increased incidence of tripping and falling. Besides toe drag, impaired gait stability in patients with CP can cause falling [12].

### Treatment

Ankle-foot orthoses are frequently used to support the impaired ankle dorsiflexors in patients with CP and to prevent deformities [13]. However, they restrict active motions and thereby exacerbate muscle weakness of the plantar flexors [14]. Functional electrical stimulation (FES) has been named as an alternative treatment as it might function as a dynamic functional orthosis [15, 16]. The definition of FES is ‘the electrical stimulation of muscles that have impaired motor control to produce a contraction to obtain a functionally useful movement’ [17]. In our systematic review, FES has been reported to increase ankle dorsiflexion during walking (change of 2–12° at initial contact and 3–11° for peak angle in swing compared to without FES), step length and ankle dorsiflexion strength, at the level of body functions and - structures. At the level of activity and participation, there is only some evidence that FES decreases the frequency of toe-drag and improves self-perceived performance and satisfaction [15]. More evidence is needed on patient centered outcome measures. Furthermore, practical guidelines for patient selection and FES settings are needed.

### Objectives

Based on our previous systematic review [15], the overall hypothesis of the present study is that FES of the ankle dorsiflexors is an alternative to AFOs in daily life for some of the patients with CP. The primary objective is to show whether FES of the ankle dorsiflexors improves activities and participation of patients with unilateral spastic CP in daily life, measured with the Goal Attainment Scale (GAS) [18]. The secondary objective is to prove whether FES is effective at the level of body functions and structures, and activities (mainly measured with gait analysis and physical examination) and the tertiary objective is to collect relevant information on acceptability, characteristics for patient selection and cost-effectiveness to decide on implementation of FES in clinical practice. We hypothesize that the proportion of goal achievement (GAS scores) in the FES phase will be 30% higher than in the conventional phase and that FES is effective in improving ankle dorsiflexion by at least 5° during walking. Regarding characteristics for patient selection, we hypothesize that FES is effective in patients with a relatively flexible ankle joint and those who are relatively physically active, because the FES stimulation is only active during walking.

## Methods

### Study design

The design of the study is a randomized crossover trial, consisting of a FES phase and a conventional therapy (mostly AFO) phase. It will be conducted at the Maastricht University Medical Center (MUMC+) in Maastricht, the Netherlands. The Medical Ethical Committee of the MUMC+ approved the study (METC azM/UM, study number 172033/NL63250.068.17). Figure 1 shows the flow chart for participants and the timing of the measurements. Four measurements will take place in total, at the start and end of every phase. Participants will take part in the study for 30 weeks. Patient recruitment and measurements will take place between August 2018 and August 2021.

**Fig. 1 Fig1:**
[figure not shown]
Flow chart of the two study arms, including the timing of measurements: 1) arm A starts with conventional therapy 2) arm B starts with FES. Abbreviations: FES: Functional Electrical Stimulation. Figure from the authors

### Participants

Subjects will be recruited from the outpatient clinics of the pediatric neurology and pediatric rehabilitation departments of the MUMC+, and collaborating centers in the region (Adelante, Center of Expertise in Rehabilitation and Audiology, Hoensbroek and Libra Rehabilitation and Audiology, Eindhoven). Individual doctors can refer patients to the MUMC+ for evaluation and participation in the study. Patients are eligible for inclusion if they are between 4 and 18 years and diagnosed with unilateral spastic CP, GMFCS level I or II (walking independently). Patients should have an unilateral foot drop of central origin with in particular the absence of initial heel contact. To avoid interference in the results of other treatments, patients are not included if they recently underwent surgery (within 1 year) or botulinum toxin injections (within 6 months). Whether the patients received injections or surgeries in the past will be reported as patient characteristic. Table 1 shows the selection criteria for participants. All participants and/or caregivers (if the participant is < 16 years) will sign an informed consent form before participating in the study. A flow chart according to the CONSORT 2010 statement will be provided showing the numbers of patient in every phase and analysis of the study [19].

**Table 1 Tab1:** Overview of inclusion and exclusion criteria for patient selection

Inclusion criteria	Exclusion criteria
• Unilateral spastic cerebral palsy	• Ankle plantarflexion contracture of > 5°with the knee extended
• GMFCS level I or II	• Botulinum toxin A injections < 6 months ago
• Age 4–18 years	• Orthopaedic surgery to the legs < 1 year ago
• Unilateral foot drop of central origin	• Uncontrolled epilepsy with daily seizures
• Treated with AFO or adapted shoes	
• Ability to walk at least 15 min	
• Confirmed cerebral abnormality on MRI	

Abbreviations: GMFCS: Gross Motor Functioning Classification System; AFO: ankle foot orthosis; MRI: magnetic resonance imaging

#### Sample size calculation

The primary outcome measure will be the GAS, a 6-point scale which will be dichotomized into ‘goal achieved’ and ‘goal not achieved’. The difference is assumed to be clinically relevant if the proportion of participants achieving the goals is 30% higher for one of the treatment phases (conventional or FES). To be able to detect such a clinically relevant difference with a power of 80%, using an alpha of 5%, we need to include at least 22 participants – based on the crossover design. Previous studies reported 0–14% dropout [20, 21]. Taking possible dropout of 14% of the participants into account, 25 participants will be included. If 10 patients completed the study, an interim-analysis will be performed to check the power for the primary outcome.

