### Primary outcome

GAS scores will be dichotomized in to ‘goal achieved’ (scores 0 to + 2) and ‘goal not achieved’ (scores − 1 to − 3). The McNemar test (non-parametric) will be applied to test whether the proportions of goal achievement are significantly different between the FES and conventional phase. Raw GAS scores will also be provided. Beside an analysis including the patients who completed the study, an intention to treat analysis will be performed including the patients who discontinued the study as ‘goal not achieved’ (‘worst case analysis’). A *p*-value of 0.05 is considered to be statistically significant in this analysis.

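### The stated 80% power at 22 completers is not supported for the two-sided McNemar test: the exact test peaks at about 69%, and other versions reach 80% only if almost no patient succeeds on conventional treatment alone

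*Protocol article*

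**What the plan says.** The Sample size calculation section dichotomises the Goal Attainment Scale and takes a 30% higher proportion of achievers, in either phase, as clinically relevant. It then states that "with a power of 80%, using an alpha of 5%, we need to include at least 22 participants", referring to the crossover design as the basis. The Objectives repeat the target in the direction of FES: "the proportion of goal achievement (GAS scores) in the FES phase will be 30% higher than in the conventional phase". Under Statistics, Primary outcome, the test is fixed: "The McNemar test (non-parametric) will be applied to test whether the proportions of goal achievement are significantly different", at a significance level of 0.05. The section on withdrawal of an individual subject makes 22 completers the floor by allowing drop-outs to be replaced.

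The document does not give an achievement rate for either phase, a discordant proportion, a within-patient correlation, the sample size formula, the sidedness of the test or the version of McNemar's test.

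**The concern.** McNemar's test uses only the discordant patients: those who achieve the goal on FES only (proportion p10) and those who achieve it on conventional treatment only (p01). A difference of 0.30 fixes p10 − p01 but not their sum, and power falls as the sum rises. The most favourable case is p01 = 0. If 22 pairs fall short of 80% there, or pass only there, the stated power is not a property of this design over most of the situations that the plan allows.

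The stake is how a non-significant primary result is read. A reader who trusts the 80% would take it as fairly strong evidence against a 30-point benefit. If the true power is much lower, that reading is not warranted. The type I error and the estimand are not affected.

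**Working it through.** **Inputs.** From the Sample size calculation: difference d = 0.30 (read as percentage points), alpha 0.05, power 80%, n = 22 pairs. The test is read as two-sided because a difference favouring either phase counts. From Primary outcome: McNemar's test. Not given, so varied: p01, with p10 = p01 + 0.30 and discordant proportion ψ = p10 + p01 = 0.30 + 2·p01. The minimum ψ is 0.30.

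**Attempt to reproduce 22.** The usual two-sided formula is n = [1.96·√ψ + 0.8416·√(ψ − d²)]² / d².
- ψ = 0.30: (1.0735 + 0.3857)² / 0.09 = 23.7, so 24.
- ψ = 0.40: (1.2396 + 0.4686)² / 0.09 = 32.4, so 33.
- ψ = 0.50: (1.3859 + 0.5389)² / 0.09 = 41.2, so 42.

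The formula does not give 22 at any admissible ψ. Other routes lead to about 22, but each needs a choice that the text does not disclose: a one-sided alpha with ψ about 0.35; a formula using only the alternative variance with ψ about 0.34 (21.8); half the parallel-group size for 35% v 65% (43/2 = 21.5); or the per-arm parallel-group size for 0% v 30% (22).

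**Best case, p01 = 0.** All discordant patients then favour FES, and their number X is binomial(22, 0.30). The test rejects once X is large enough.
- Exact: five of five gives p = 2·0.5⁵ = 0.0625, six of six gives 0.031, so X ≥ 6 is needed. P(X ≥ 6) = 68.7%.
- Mid-p: five of five gives 0.031, so X ≥ 5 is needed. P(X ≥ 5) = 83.5%.
- Uncorrected chi-square: four of four gives 4²/4 = 4.0, above 3.84, so X ≥ 4 is needed. P(X ≥ 4) = 93.2%.

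For the exact test at p01 = 0, P(X ≥ 6) is 77.1% with 24 pairs and 80.7% with 25, so 25 are required.

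**General case.** Power at 22 pairs was enumerated over the number and direction of discordant pairs:

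| p01 | p10 | ψ | Exact | Mid-p | Uncorrected |
|---|---|---|---|---|---|
| 0 | 0.30 | 0.30 | 68.7% | 83.5% | 93.2% |
| 0.01 | 0.31 | 0.32 | 64.6% | 78.6% | 85.1% |
| 0.0175 | 0.3175 | 0.335 | 61.8% | 75.3% | 80.1% |
| 0.02 | 0.32 | 0.34 | 60.9% | 74.3% | 78.6% |
| 0.05 | 0.35 | 0.40 | 51.9% | 63.7% | 64.8% |
| 0.10 | 0.40 | 0.50 | 41.3% | 51.3% | 51.4% |

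The continuity-corrected test agrees with the exact test to within 0.5 points over this range. The limit of 0.0175 for the uncorrected test means an expected 22 × 0.0175 = 0.4 patients who achieve the goal on conventional treatment only.

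**Detectable difference.** For 80% power at 22 pairs and p01 of 0.05 to 0.10, the difference must be 43 to 50 points (exact) or 38 to 45 points (uncorrected).

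**The case against.** The strongest reply is that neither p01 nor the McNemar version is stated, and that some combinations do deliver the claim. At p01 = 0, mid-p gives 83.5% and the uncorrected test 93.2%; the uncorrected test would need only 18 pairs there. A low p01 is also arguable from the design. Conventional treatment is what the patient already receives, the baseline situation is scored −2 (two levels below the goal), and one of the two goals is chosen to reflect FES treatment. That the Objectives see FES as an option for only some patients does not imply p01 > 0, since a patient whom FES does not help may fail in both phases. This stands: a reader might infer that 22 can never give 80%, or that the realistic power is 40% to 65%, and the document supports neither, because both depend on unstated quantities.

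A second reply is that a journal article may leave discordance assumptions and test version to the full protocol or analysis plan. That would answer a complaint about missing detail. It does not answer a figure that the article does state, for a named test at a named number of patients, and that fails over nearly all admissible values.

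A third is that two goals per patient could supply 44 pairs, with exact power of about 83% at ψ = 0.46. The sample size text counts participants, however, and two goals in one child are not independent.

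Three further inferences are not supported. Enrolling 25 might look too few for 14% dropout (22/0.86 = 25.6), but the replacement rule secures 22 completers. A relative reading of 30% needs a baseline rate that the document does not give. Nothing says that the power check after 10 completers would reuse the original assumptions.

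**Conclusion.** The point holds in conditional form. For a two-sided McNemar test and a 30-point difference, 22 completers cannot reach 80% with the exact or continuity-corrected version; the ceiling is 68.7%. With the uncorrected version, 80% requires p01 of about 0.0175 or less, and with mid-p, p01 below about 0.01. The stated power therefore survives only at or near minimum discordance and only with a version that the plan does not name.

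How far power falls short depends on assumptions made here. With p01 assumed at 0.05 to 0.10, it is 52% to 41% (exact) or 65% to 51% (uncorrected). These values illustrate the sensitivity and are not an estimate of this trial's power. The conclusion also rests on reading 30% as percentage points and the test as two-sided.

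**What to change.** In the Sample size calculation, state that 30% means percentage points, give the assumed p10 and p01, and name the version of McNemar's test, using the same version under Primary outcome. Then either restate the power at 22 completers (at most 69% with the exact test, shown over a range of p01) or keep 80% and restate the difference that 22 completers can detect under the stated assumptions.

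The cost is a reworded paragraph and a less favourable power statement. No extra patients are needed, and the design and primary outcome do not change.

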### Randomization and blinding

Subjects will be randomly assigned to start with either FES or conventional treatment. The randomization by blocks of four is based on even and uneven numbers, in envelopes created by the independent expert using www.random.org/sequences. Blocks of four are applied to ensure an equal distribution of the study phases over time which is important for FES device availability: of every four patients starting the trial, two will start with FES and two will start with the conventional therapy. The envelope will be opened once the patient has been included in the study, at the end of the intake appointment.

Blinding patients to the FES treatment is not possible, as most patients feel the electrical stimulation and obvious elicited muscle contractions are necessary for proper set-up. However, blinding of an assessor is possible: the physiotherapist (SF) that performs physical examination at every time point and assesses the GAS, will be blinded for the treatment phase. Patients and parents will be informed about the blinding procedure and instructed to take off the walking aid before visiting the physiotherapist.

### Intervention

This study will compare FES of the ankle dorsiflexors during walking to conventional treatment (AFO and/or adapted shoes).

#### FES treatment

FES of the ankle dorsiflexors will be applied using the WalkAide device (Innovative Neutronics, Austin, Texas, USA, from now on: ‘FES device’) with surface electrodes. Patients will wear the device for 12 weeks in their own living environment. Patients who have a compensation for leg length difference or arch support in their AFO, will be supplied with appropriate leg length - or arch support in the form of shoe-inlay during the FES phase. If applicable, physiotherapy can be continued as in the normal situation.

The FES device stimulates the common peroneal nerve, activating the dorsiflexor muscles of the foot during the swing phase of gait. The timing of the electrical stimulation during walking is decided by a tilt sensor that measures the inclination and the acceleration of the leg. Therefore, the FES device should be worn on the leg, just below the knee as specified below.

#### Procedure FES set-up

At the start of the FES phase, there will be an individual FES set-up meeting per patient with the physiotherapist and physician (hereafter called: the therapist, ‘he’), consisting of:Electrodes positioning

The patient receives an explanation regarding the procedure. Next, the therapist identifies the head of the fibula while the patient is in supine position and he marks it with a moon-shaped line inferior-posterior of the bone. He moistens this area and uses the MiniStim peripheral nerve stimulator to identify the location with the best motor-response of the tibialis anterior muscle, by moving the MiniStim along this line, while applying a bit of pressure and gradually increasing the current. In general, a dorsiflexion motor response is needed, eventually with a bit of eversion. The therapist puts his hand on the tibialis anterior muscle to feel if contraction occurs, and marks the appropriate stimulation place. This is the position for the black electrode of the FES device, over (the deep branch of) the peroneal nerve. The red electrode is placed on the upper 1/3 of the tibialis anterior muscle belly. The therapist checks the motor response with the ‘stimulation’ button of the FES device and adjusts the electrodes position if necessary. It should be kept in mind that pressure applied on the electrodes can influence the effect.2.Fitting of the device

The therapist places the cuff of the FES device (including Velcro electrode locators) over the electrodes and the device on the medial side of the lower leg. The orange indicator in the cuff (Fig. 2) should point to the middle of the patella. The position of the indicators (top and bottom of the WalkAide cuff) is marked with a surgical skin marker, to help the patient or parents put it in the correct position.3.Timing of the stimulation

**Fig. 2 Fig2:**
[figure not shown]
The WalkAide device positioned on the leg. The orange indicator at the top is visible. Image:© 2020 Innovative Neurotronics, Inc., All rights Reserved. Usage in paper allowed

Surface electromyography (sEMG) is used to evaluate the timing of the stimulation during the gait cycle. This is more precise than relying on the ‘auditive feedback’ from the WalkAide device that can be turned on to hear the timing of the stimulation during walking. With a quick set-up of three markers on the foot (caput of metatarsal bone 2 and 5 and the heel) and one sEMG sensor on the tibialis anterior muscle, the on/off timing of the stimulation during the gait cycle can be visualized in a 3D gait laboratory. This set-up is not used for gait analysis but only for evaluation of the timing of the stimulation. Figure 3 shows the FES stimulation in the EMG as big spikes. The goal is to let the stimulation start just after toe-off and let it stop just after heel strike. In the WalkAnalyst software, it is possible to adjust the thresholds for on/off and the durations of stimulation and no stimulation.4.Stimulus intensity

